### Interim analyses {21b}

To provide confidence that our trial will be well powered at completion, we will perform an interim analysis for re-estimation of the sample size at approximately 50% information (*N* ≈ 63). The sample size re-estimation will be based on a conditional power approach as described by Mehta and Pocock [48]. The proposed approach allows for incorporation of an unblinded sample size re-estimation without inflating type I error. If the estimate of conditional power at interim analysis is within the pre-defined promising zone, we will consider an increase in the total sample size. If conditional power is outside the promising zone, we will continue with the planned sample size. The promising zone defines a range at which interim conditional power is below the unconditional power targeted during study design, but high enough that increasing the sample size at or below the maximum feasible sample size will recover the targeted power. Increasing the sample size only if the conditional power falls within this range preserves type I error for final analyses. Detailed results of the interim analysis will be kept securely with the unblinded DCC team. There will be no formal stopping rules for efficacy or safety. Adverse events (AEs) and serious adverse events (SAEs) will be recorded on dedicated case report forms and will be reviewed on an ongoing basis by the DSMB. The trial may be stopped early for safety at the recommendation of the DSMB.

### Methods for additional analyses (e.g., subgroup analyses) {20b}

Exploratory analyses will also assess heterogeneity of treatment effects by planned sub-groups. Specifically, separate models will be built and the interaction term between treatment and each individual sub-group (i.e., age group (> 65 vs 18–65), sex, prior hospitalization, prior biologic and/or small molecule exposure) will be included in the logistic regression model, described in primary analyses. Depending on the distribution of categorical variables, binary variables may also be considered.

Planned sub-groups:Age (> 65 years versus 18–65 years)Gender (male versus female)Prior hospitalization for an ulcerative colitis flare (yes versus no)Prior biologic and/or small molecule exposure (yes versus no)Number of prior biologic and/or small molecule exposures (0, 1, 2, 3 or more)Type of biologic and/or small molecule being used at time of hospitalizationSteroid dependent and/or resistant at the time of hospitalization (yes versus no)Baseline endoscopic severity (Mayo endoscopic subscore of 2 versus 3)Baseline C-reactive protein (< 5 mg/L versus ≥ 5 mg/L)Steroid type during hospitalization (methylprednisolone versus hydrocortisone)Chamber type during trial (monoplace versus multiplace)Day 3 response status during trial (day 3 responder versus non-responder)

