### Objectives {7}

The primary objective of the HBOT-UC trial is to confirm the ability of HBOT to improve clinical response to steroids, while avoiding need for biologics, small molecules, or colectomy in-hospital, in UC patients hospitalized with moderate to severe flares. The secondary objective is to assess the long-term durability of treatment effect over 12 months, and to further investigate the effects of HBOT on additional key patient reported outcomes and histo-endoscopic measures of disease activity. Additional exploratory objectives are to assess treatment effect heterogeneity by subgroups of interest and to assess differences in intestinal ultrasound measures of disease activity. This will serve as a basis for explaining or supporting findings from primary analyses and for further investigating whether treatment effects may vary for different subgroups.

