### Sample size {14}

Sample size estimates were based on the primary aim of detecting a clinically meaningful increase in the frequency of clinical response/remission in the HBOT arm compared to the control arm. Specifically, we estimate that our primary outcome will be achieved in 30% of hyperbaric oxygen treated patients and in 10% of sham hyperbaric air treated patients. Based on combined phase 2 A and 2B trial data, we found 11 of 22 (50%, 95% CI: 28–72%) patients who received the HBOT achieved normalization of rectal bleeding and improvement in stool frequency [28, 29]. Given the small sample sizes of these trials, we have chosen the lower bound of this confidence interval (30%) for the point estimate of the primary outcome in the HBOT arm. Outpatient moderate-severe ulcerative colitis trials have observed a 10% placebo response rate for resolution of rectal bleeding by day 5 of active therapy. Although our population being recruited is sicker and the anticipated placebo/sham response rate would be lower than seen in outpatient trials, we have chosen a conservative estimate of 10% for the primary outcome in sham treated patients. For 80% power, with 1:1 randomization and a 5% two-sided significance level, we estimate we will need 63 patients per arm to detect an absolute difference in clinical remission of 20% (30% in HBOT arm vs. 10% in Sham), based on the standard sample size calculation formula for a two-sample test of proportions.

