### Methods in analysis to handle protocol non-adherence and any statistical methods to handle missing data {20c}

A sensitivity analysis will be conducted on the per-protocol sample including participants who (1) completed at least 3 full, consecutive intervention sessions, where a “full” session is defined as at least 60 min under pressure; (2) do not have an “early” colectomy, defined as a colectomy on or before day 3; and (3) do not have protocol deviations for unacceptable treatment adjustments through day 3. Results will be used to complement the primary planned analyses based on the intention-to-treat sample.

Given the short time frame and nature of hospitalization, we do not expect any attrition for the primary endpoint. For secondary analyses beyond day 5, we do anticipate larger dropout. In the event of large amounts of missing data (i.e., more than 10%), multiple imputation analyses will be explored. Mechanisms of missing data will be examined, with an assessment of variability in missing rate by participant characteristics. These summarizations will inform potential biases resulting from missing data. If appropriate, multiple imputation methods will be considered in sensitivity analyses. Results will be compared across approaches to assess the effect of missing data, robustness to various model specifications, and validity of specified models.

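### Age and baseline CRP enter the exploratory interaction tests only as two-level groups; testing them as continuous would keep more information if the HBOT effect changes gradually, at almost no cost

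*Protocol article*

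**What the plan says.** Heterogeneity is an exploratory aim. Under Objectives {7}: "Additional exploratory objectives are to assess treatment effect heterogeneity by subgroups of interest". The method is in Methods for additional analyses {20b}: "separate models will be built and the interaction term between treatment and each individual sub-group" goes into the logistic model of the primary analysis, which adjusts for bio-naïve or bio-exposed status.

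Two of the twelve listed sub-groups are cut from continuous measurements. One is age, over 65 against 18–65. The other is "Baseline C-reactive protein (< 5 mg/L versus ≥ 5 mg/L". No continuous version of either is described. The only allowance for uneven groups is "Depending on the distribution of categorical variables, binary variables may also be considered", which does nothing for a variable that is already binary.

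Elsewhere CRP is treated as continuous. Under Outcomes {12} it is a key secondary endpoint summarised as a mean, and under Statistical methods {20a} its mixed model adjusts for the corresponding baseline measure.

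**The concern.** Cutting a continuous modifier treats everyone on one side of the cut as alike. If the benefit of HBOT rises or falls steadily with inflammatory burden or age, that throws away information the database already holds, in a trial with few responders to begin with. The cut can also create a small group. If that group has no responders in one arm, the standard fit gives no finite interaction odds ratio and no usable Wald interval.

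At stake is how well the trial can answer its exploratory question of whether benefit varies between patients. The primary conclusion does not depend on it.

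**Working it through.** **Inputs from Sample size {14} and the missing-data section {20c}.** "we estimate that our primary outcome will be achieved in 30% of hyperbaric oxygen treated patients and in 10% of sham hyperbaric air treated patients"; "For 80% power, with 1:1 randomization and a 5% two-sided significance level"; "we estimate we will need 63 patients per arm"; and "we do not expect any attrition for the primary endpoint".

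**Plan's own figure.** The pooled-variance formula for 30% against 10%, two-sided 5% and 80% power gives 62 per arm (59 unpooled, 72 with continuity correction). With 63 per arm the power is 0.809. The stated 63 is reproduced.

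**Expected responders.** 63 × 0.30 + 63 × 0.10 = 18.9 + 6.3 = 25.2.

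**Empty-cell probability.** The article does not give the share over 65 or the share with CRP below 5 mg/L, so the smaller group's share q is an assumption, varied from 5% to 50%. Response rates are taken as equal in both sub-groups. Two counts are useful:

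- Smaller group only, with n = 63q rounded: P = 1 − (1 − 0.9^n)(1 − 0.7^n).
- All four arm-by-group cells, with random group membership: a cell holding share s of an arm with response rate p is empty with probability (1 − s·p)^63, and the cells are then combined.

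| Share q | n per arm | Expected sham responders (6.3q) | Smaller group | Any of four cells |
|---|---|---|---|---|
| 5% | 3 | 0.3 | 82% | 83% |
| 10% | 6 | 0.6 | 59% | 60% |
| 20% | 13 | 1.3 | 26% | 30% |
| 30% | 19 | 1.9 | 14% | 16% |
| 50% | 32 | 3.2 | 3% | 8% |

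Example at 20%: 0.9^13 = 0.254 and 0.7^13 = 0.010, so P = 1 − 0.746 × 0.990 = 0.26. The sham cell drives the result.

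**Information kept by a cut.** For a normally distributed modifier with a linear effect, the ratio is φ(c)²/[q(1 − q)], where c is the cut point in SD units: 64% at 50/50, 49% at 80/20, 34% at 90/10 and 22% at 95/5.

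**Interaction power.** Simulated trials of 126 patients, with a likelihood-ratio interaction test at 5%, adjusted for a 50/50 stratum. Log-odds of response are set to 10% in sham and to 30% in HBOT at the modifier mean; the modifier acts in HBOT only. The slopes are assumptions.

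| Slope per SD | Continuous | Cut (smaller group 10–50%) |
|---|---|---|
| 0.7 | 27–30% | 16–21% |
| 0.8 | 32–37% | 19–26% |
| 1.0 | 43–48% | 24–33% |

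If the effect instead steps at the cut (assumed log-odds step of 1.5), the order reverses: about 24–26% continuous against 33–34% cut at 50/50, and 17% against 30% at 80/20.

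**The case against.** The strongest reply is that nothing here is false or contradictory. The stated aim is heterogeneity by sub-groups, cut points fixed in advance rule out data-driven ones, and no claim or error rate depends on exploratory tests. A condensed article need not justify its cut points. All of that stands, and it limits the point to an improvement in method.

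A reader might infer more than the documents support, in four ways:

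- **That empty cells will be frequent.** This depends on shares the documents do not give. It is fair at about 20% or less and wrong near an even split.
- **That the interaction then cannot be analysed.** Only the ordinary maximum-likelihood odds ratio fails. A likelihood-ratio test or a penalised fit still works, and the article does not commit to Wald inference; that detail may sit in the analysis plan.
- **That the cuts cause the sparsity.** About 25 responders is thin for every sub-group on the list, most of them inherently categorical.
- **That a fixed fraction of information is lost.** The ratios above need a normal modifier and a linear effect. The documents do not say which shape applies, and a true step favours the cut.

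It is also fair to note that the sentence describing the interaction model names age, sex, prior hospitalisation and prior exposure. CRP appears in the longer list of planned sub-groups that follows, so its place in that model is the natural reading but is not spelled out. The general allowance in {20a} for transformations or higher-order terms applies when model assumptions are in question; it does not say that these two modifiers will be analysed as continuous.

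**Conclusion.** The point holds as a minor improvement to an exploratory analysis. For age and baseline CRP a continuous test is available from data already collected. Under a gradual effect it raises interaction power from about 19–26% to about 35% at a slope of 0.8 per SD, and it removes the dependence on a possibly small group. The empty-cell risk is 26–82% for shares of 20% down to 5%, and 3–8% at an even split.

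The size rests on assumed slopes, a normal modifier, assumed shares and the plan's 30% and 10% response rates. Even with the change the tests remain underpowered.

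**What to change.** In Methods for additional analyses {20b}, state that the exploratory interaction tests for age and baseline CRP (log scale) use the continuous value in the existing logistic model: treatment, modifier, treatment-by-modifier and the stratification factor. Report the estimated treatment effect with its confidence interval at stated values of each modifier. Keep the 65-year and 5 mg/L groups as a descriptive or supporting display, with responder counts by arm.

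The cost is a sentence or two of wording, with no new data, patients or procedures. The downside is an assumed log-linear interaction, which about 25 responders can check only weakly; the retained cuts give some view of a step. The change does not solve sparsity in the inherently categorical sub-groups.

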Hyperbaric oxygen therapy (HBOT) targets mechanisms central to the pathogenesis of UC and mucosal integrity. Mechanisms thought to play a role in UC include (1) a dysregulated response to tissue hypoxia with altered barrier function; (2) an aberrant host response to gut flora with shifts in microbial composition; and (3) recruitment and activation of neutrophils and pathogenic T cells in the bowel leading to cytokine production and inflammation [14–20]. HBOT involves breathing 100% oxygen under pressure to increase plasma and tissue oxygen levels. The high levels of oxygen created by HBOT have been shown to produce a variety of downstream effects that persist well after the participant leaves the chamber which include (1) reductions in inflammation and inflammatory cytokine production, (2) interfering with neutrophil trafficking to target tissues, (3) shifts in host-microbiome metabolism and microbial composition, (4) stabilization of hypoxia response pathways (HIF-1α, HO-1), and (5) increased growth factor synthesis and stem cell migration to improve wound healing [21–27]. HBOT may therefore offer a promising new treatment as it targets several of the mechanisms involved in UC pathogenesis [26].

A meta-analysis across 17 studies of patients with Crohn’s disease (*n* = 286) or UC (*n* = 327) provided evidence of safety and potential efficacy for treating inflammatory bowel disease (IBD) patients [26]. IBD patients treated with HBOT had an overall response rate of 86%. Analyses limited to studies with endoscopic follow-up indicated an overall response rate for UC patients of 100%. HBOT was also well tolerated by IBD patients, with adverse event rates (10 per 10,000 HBOT sessions) and serious adverse events (6 per 10,000 sessions) being rare. Separate Phase 2 A and Phase 2B multicenter, randomized, sham-controlled trials were conducted to provide preliminary evidence in support of HBOT for UC. In the Phase 2 A trial, the treatment effect benefit was primarily seen in the first 3 days of therapy, with maximal benefit achieved by day 5 (day 5 clinical remission: 50% HBOT vs 0% Sham, *p* = 0.04) [28]. A subsequent Phase 2B trial demonstrated that five HBOT sessions (compared to three) were needed to achieve maximal clinical benefit [29].

Given the minimal risks associated with HBOT and preliminary evidence of clinical improvement in UC patients with HBOT, a larger trial is warranted to confirm efficacy.

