### Outcomes {12}

The primary outcome is clinical response, a binary indicator measured by complete resolution of rectal bleeding (Mayo rectal bleeding sub-score of 0) and improvement in stool frequency (at least 1 point reduction in Mayo stool frequency), without the need for biologics, small molecules, or colectomy assessed at day 5. If a participant is discharged prior to day 5, any biologics or small molecules taken after discharge do not contribute to the endpoint definition. Additionally, participants who are discharged before day 5 with complete resolution of rectal bleeding and improvement in stool frequency, without the need for biologics, small molecules, or colectomy will be considered as clinical responders regardless of day 5 assessments. Data will be summarized as the proportion meeting the clinical response definition.

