Key secondary outcomes include (1) clinical response, a continuous measure of the sum of Mayo rectal bleeding and stool frequency sub-scores summarized as the mean at day 3; (2) C-reactive protein (CRP), a continuous measure summarized as the mean at day 3; and (3) endoscopic response, a continuous measure defined by the Ulcerative Colitis Endoscopic Index of Severity (UCEIS) summarized as the mean at day 5. Additional secondary endpoints include (1) steroid-free, colectomy-free, clinical remission (Full Mayo score ≤ 2, with no sub-score > 1), a binary indicator summarized as the proportion at day 90; (2) endoscopic improvement, a binary indicator defined by a Mayo endoscopic sub-score of 0 or 1 summarized as the proportion at day 90; (3) endoscopic remission, a binary indicator defined by a Mayo endoscopic sub-score of 0 summarized as the proportion at day 90; (4) mucosal healing, a binary indicator defined by a Mayo endoscopic sub-score of 0 or 1 and a Geboes histology score ≤ 2 summarized as the proportion at day 90; (5) clinical remission, a binary indicator defined by a full Mayo score ≤ 2 with no sub-score > 1 summarized as the proportion at day 5; (6) need for colectomy, a binary indicator summarized as the proportion at day 90 and (7) the proportion at 12 months; (8) Re-hospitalization for an ulcerative colitis flare, a binary indicator summarized as the proportion at 12 months; (9) Urgency Numeric Rating Scale (NRS), a continuous measure summarized as the mean at day 3; and (10) any serious infection or serious adverse event, a binary indicator summarized as the proportion at day 5. Of note, continuous outcomes violating normality assumptions may be summarized with medians.

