## Statistical methods

### Statistical methods for primary and secondary outcomes {20a}

Primary analyses will be based on an intention-to-treat principle, whereby all patients will be analyzed as randomized. Descriptive statistics will summarize all baseline variables by arm, and there will be no formal hypothesis testing for comparison of baseline characteristics between treatment arms. Standardized differences in covariates may be examined to evaluate covariate balance across groups. Residual diagnostics will be examined, and relevant assumptions will be assessed using graphical display and statistical testing where appropriate. In situations where modeling assumptions are in question, nonparametric methods, transformations, or inclusion of higher-order terms may be applied.

Primary analyses will employ a logistic regression model to estimate the odds of clinical response in the treatment arm compared to the control arm, adjusting for the stratification factor (bio-naïve or bio-exposed). The odds ratio and 95% confidence interval will be reported with the corresponding p-value.

A linear mixed model will be used for key secondary continuous endpoints (clinical response and CRP), incorporating data from daily assessments (day 2 and day 3). Specifically, the mixed model will include fixed effects for arm (HBOT vs. sham), timepoint (visit day), the interaction between arm at timepoint (to allow for different differences between arms at each visit), corresponding baseline measure, and the stratification factor. For both endpoints, the hypothesis of interest will be based on the difference in score at day 3. For UCEIS (not assessed daily), a linear model will be used to estimate the difference in mean UCEIS score at day 5 between arms adjusting for baseline UCEIS and the stratification factor. In primary analyses, participants with an early colectomy preventing assessment of UCEIS at day 5 will be excluded from the analysis. A correction for multiple testing of the three key secondary endpoints will be incorporated using the Holm method.

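### Day-3 response status, measured during treatment and expected to respond to it, is planned as a treatment-effect subgroup; arm comparisons within it are not randomised

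*Protocol article*

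**What the plan says.** All references are to the protocol article.

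- **Methods for additional analyses {20b}** sets the purpose: "Exploratory analyses will also assess heterogeneity of treatment effects by planned sub-groups". The method is that "separate models will be built and the interaction term between treatment and each individual sub-group" goes into the primary logistic model. Twelve planned subgroups follow; the last is "Day 3 response status during trial (day 3 responder versus non-responder". It has no separate method and no caveat.
- **Statistical methods {20a}** defines the model being extended: "Primary analyses will employ a logistic regression model to estimate the odds of clinical response in the treatment arm compared to the control arm", adjusted for prior biologic exposure.
- **Outcomes {12}** defines the primary outcome as resolved bleeding with improved stool frequency, "without the need for biologics, small molecules, or colectomy assessed at day 5". The same section makes a day-3 measure a key secondary efficacy endpoint: "clinical response, a continuous measure of the sum of Mayo rectal bleeding and stool frequency sub-scores summarized as the mean at day 3".
- **Background and rationale {6a}** reports of the Phase 2A trial that "the treatment effect benefit was primarily seen in the first 3 days of therapy".
- **Participant timeline {13}** places the intervention on five consecutive days after randomisation, so day 3 falls during treatment.

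**The concern.** A subgroup factor can show effect heterogeneity only if treatment cannot alter it. Then the patients in each subgroup are still randomised between arms. Day-3 response does not meet that condition here: it is observed after several sessions, and the article itself expects treatment to move it.

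If treatment does move it, day-3 responders on hyperbaric oxygen include patients who responded because of treatment, while sham responders got there without it and have better prognosis on average. Non-responders are selected in the same way: those still unresponsive on active treatment are a harder group than those unresponsive on sham. Any benefit already delivered by day 3 is also conditioned away.

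What is at stake is the reading of this one exploratory result. A treatment that works could look neutral or harmful in both strata, and an interaction could appear, or fail to appear, for reasons unrelated to who benefits.

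**Working it through.** **The plan's own figure.** The article gives no number for this analysis. The nearest is the sample size for 30% versus 10%, 80% power, two-sided 5%. With pooled variance:

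n = [1.96·√(2·0.2·0.8) + 0.8416·√(0.3·0.7 + 0.1·0.9)]² / 0.2² = (1.109 + 0.461)² / 0.04 ≈ 61.6, so 62 per arm.

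The stated 63 agrees and gives power 0.81. Nothing below changes it. The planned overall odds ratio is (0.30/0.70)/(0.10/0.90) = 3.86.

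**Model.** Let U ~ N(0,1) be unobserved prognosis, R day-3 response and Y day-5 response.

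- logit P(R=1) = a(arm) + s·U
- logit P(Y=1) = b + s·U + g·R + d·arm

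The value s sets how strongly prognosis drives both days, g the dependence of day 5 on day 3, and d any further treatment effect. There is no treatment-by-R term, so no interaction is built in. Odds ratios by R come from numerical integration over U.

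**Inputs.** From the article: the 10% and 30% day-5 rates. Assumed, because the article gives none: sham day-3 response 20%, active day-3 response 30-50%, s = 1 to 3, and g = 2 (g = 0 in scenario C).

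| Scenario | Overall OR | OR, day-3 responders | OR, non-responders | Ratio of ORs |
|---|---|---|---|---|
| A. Effect only through day 3 (d = 0) | 1.16 to 1.74 | 0.91 to 0.40 | 0.92 to 0.24 | 1.00 to 1.69 |
| B. Overall 30% v 10% (d solved for) | 3.86 | 4.98 to 1.63 | 8.23 to 2.08 | 0.61 to 0.90 |
| C. Day-3 response 20% to 40%, no day-5 effect | 1.00 | 0.84 to 0.52 | 0.85 to 0.41 | 0.98 to 1.27 |
| Control: no effect on day 3 or day 5 | 1.00 | 1.00 | 1.00 | 1.00 |

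**One case in full** (A, s = 2, active day-3 response 40%):

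- Responders: 31.3% v 41.7%, OR = (0.313/0.687)/(0.417/0.583) = 0.64.
- Non-responders: 1.2% v 2.1%, OR 0.59 from unrounded rates.
- Whole arms: 0.4·0.313 + 0.6·0.012 ≈ 0.13 on active, against 0.2·0.417 + 0.8·0.021 ≈ 0.10 on sham. The overall OR is 1.38 from unrounded rates.
- Ratio of ORs: 0.64/0.59 ≈ 1.09.

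Both strata point to harm, yet the whole arms show benefit and treatment does nothing after day 3 in this model.

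**Reading the interaction column.** In A the ratio stays at 1.00 to 1.01 for s = 1, and runs from 1.14 to 1.69 for s = 3. In B the values below 1 need care. When treatment leaves day-3 response unchanged at 20%, the ratio is already 0.87, 0.75 and 0.67 for s = 1, 2 and 3, because odds ratios change when averaged over prognosis. Most of the shortfall in B is therefore non-collapsibility and not selection. Either way, a ratio away from 1 in either direction does not show that treatment acts differently in the two groups.

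**The case against.** **The analysis is exploratory.** It is one of twelve factors, and nothing in the article ties a decision rule, an error allocation or the sample size to it. That limits severity. It does not cure the problem: the label warns about power and multiplicity, while the defect here is that the contrast is not randomised.

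**The interaction test may be nearly unaffected.** A reader might infer that the interaction test is always biased. The documents and the calculation do not support that. With weak shared prognosis the ratio is about 1.0, and in the control case nothing is distorted. The stratum odds ratios are the firmer problem, and the article names only the interaction term; stratum estimates follow from that model but are not promised.

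**The article may not mean this factor.** The parenthesis illustrating the interaction method names four factors, none of them measured during treatment. But the method refers to "the interaction term between treatment and each individual sub-group", and the full list stands under the same heading, so inclusion is the natural reading. The article does not define a day-3 responder. The point does not depend on the exact definition, only on the status being observed during treatment.

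**The magnitudes are assumed.** They are. The article gives no day-3 response rates and no measure of prognostic strength. The ranges show what can happen; they are not forecasts.

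**Conclusion.** The point stands in a limited form. A variable observed during treatment, which the article expects treatment to change, is set up as a factor for heterogeneity of treatment effect. If hyperbaric oxygen affects day-3 response, comparisons within day-3 strata are not randomised. Under the assumptions above, an effect acting only through day 3 turns an overall odds ratio of about 1.2 to 1.7 into stratum odds ratios of about 0.9 down to 0.2. At the planned 30% versus 10%, both strata would still favour active treatment, but their odds ratios (1.63 to 8.23) would not measure who benefits more. Distortion of the interaction ratio depends on the strength of shared prognosis and should not be asserted without that condition.

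Two stronger inferences lack support. The primary analysis, its type I error and N = 126 are untouched. A reader might also suppose that the result would decide who continues sessions after day 3, but the article proposes no such rule and plans five consecutive days for everyone.

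**What to change.** Remove day-3 response status from the planned subgroup and interaction list in {20b}, and make the matching change in the full protocol and analysis plan if they carry it. If the pattern is of interest, tabulate day-5 outcome by day-3 status within each arm, with no arm comparison, labelled as descriptive and not as effect heterogeneity.

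Eleven of the twelve factors remain. The change is a line or two of text; the data collected, the sample size, the error rate and the primary analysis stay as they are.
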